## Methods

### Trial design and setting

This is a single-centered, partially randomized placebo-controlled double-blind feasibility trial with three intervention arms (Gutopia, Gutboost, and Gutless) and one active control. In total, 100 pregnant women with a history of depression and/or anxiety/PDA attending Sunnybrook Hospital Clinics in the Greater Toronto Area will be recruited.

Participants in Gutopia will receive a daily dose of both investigational products and dietary counseling on increasing dietary fiber. Participants in Gutboost will receive a daily dose of both investigational supplements, while participants in the Gutless arm will receive fish oil and a placebo. Participants in Gutless and Gutboost will be blinded to the status of the placebo/probiotic they will be receiving. The study member interacting with the patients will also be blinded to the treatment group the participant is assigned to. Participants who fully consent to receiving both investigational products, including placebo, will be fully randomized to one of the intervention arms. Participants not willing or able to take a placebo or probiotics will be assigned (not randomized) to the appropriate group that accommodates their preferences/needs. Participants unable or unwilling to take any of our investigational products will be assigned to the active control arm. Women in the control arm will receive standard care offered to all obstetric patients seen at the hospital.

The study involves six study visits, all of which can be conducted virtually every 3 months from the time of enrollment (**Figure 1**). The last study visit will happen between 9 and 12 months postpartum. Two of the study visits will occur during pregnancy [enrollment (visit 1) and third trimester (visit 2)], with the remaining occurring at 1, 3, 6, and 9 months postpartum. At all study visits, information on diet, mental health, physical activity, and sleep quality will be collected. Additionally, all participants will provide a stool sample at each visit, using our stool collection kits, which will be shipped to or dropped off at our center.

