#### Criteria for study withdrawal

All eligible participants will be informed that their participation is completely voluntary, and they can discontinue participation at any time. Participants may withdraw from the study entirely or from specific parts of the study only. If the latter is desired, then follow-up pertaining to other consented components of the study will continue.

Data collected prior to withdrawal may be retained and used in a manner consistent with the study purpose and protocol. The exception is if participants explicitly request the removal of all previously collected information and data, in which case the study team will oblige. Once a participant expresses a desire to withdraw from the study, the research team member in contact with the participant will confirm whether previously collected data can be retained (or should be destroyed) and whether the participant can be contacted in the future for other research opportunities.

The participant will be notified during consent and at the time of withdrawal that any data retained for the analysis cannot be withdrawn after study closure or publication of the study (whichever comes first). Lost to follow-up is defined as enrolled participants that were randomized and completed all parts of visit 1, but completed zero parts of any subsequent visits (2, 4–7). Five attempts will be made to reschedule the study visits for these participants. The number of attempts and modes of communication to reach these participants will be documented. If the missed study visit is not successfully rescheduled within 4 weeks, the visits will be marked as lost to follow-up. Should the participant return to completing the later visits, they will be included in all analyses consistent with the intention to treat. However, if all attempts to reconnect by the study team fail for the missed visit and all remaining visits, and/or if the participant explain that they wish to stop participating in the study, they will be marked as study withdrawal.

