All adverse events during the study period will be recorded, and these records will be maintained for 15 years. The clinical trial sponsor will inform the Natural and Nonprescription Health Product Directorate of Health Canada of any serious expected or unexpected adverse events related to the study product immediately if possible and no later than 7 days after becoming aware of the information. Reported symptoms of psychosis (hallucinations, delusions, or disordered thinking) will trigger a referral of participants to the study psychiatrist for assessment and to determine whether they meet the criteria for withdrawal. If a participant reports a significant worsening in symptoms of anxiety or depression, they will be permitted to remain enrolled in the study but will be advised to contact their primary mental healthcare provider for assessment and management. If the mental healthcare provider suggests that psychiatric rescue medication is needed, this clinician will recommend the treatment to the participant. Changes to treatment regimens must be reported to the study team for documentation.

Serious adverse events will also be reported to the research ethics boards that have reviewed the study protocol.

Participants who complete all parts of the study but fail to adhere to regular supplemental intake (defined as missing 7 or more consecutive days), will be included in the study for as long as they wish. Their reasons for not taking the supplements will be documented, and strategies to help overcome this (i.e., forgetfulness) will be made. If the reasons for stopping supplements are allergic reactions or side effects, they will be withdrawn from the intervention, and an adverse report will be made consistent with the safety protocol. If participants still wish to continue with the study, they may do so as part of the control arm.

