#### Statistical analysis

Should the trial succeed and we continue to recruit for a larger trial, the following statistical plan will be used to compare mental health outcomes between the groups: we will use mental health scores as the primary outcome and an intent-to-treat approach for these analyses.

Participants lost to follow-up will be assumed to have lost interest/commitment to the study and will be excluded from the analysis. Those who discontinue treatment will still be included.

Between-group differences for EPDS/GAD-7 scores will be analyzed using analysis of covariance (ANCOVA), with group membership as the independent variable, EPDS/GAD-7 as dependent, and pharmacotherapy, exercise status, and any form of psychotherapy as covariates.

The interaction effect between the O3FA and probiotics model will be analyzed and reported in each model. Alternative models will be used if the assumptions of ANCOVA are violated. If differences are found between groups, appropriate *post-hoc* analyses will be conducted to identify where the differences lie. Within-group differences at each time point will be analyzed using repeated measures ANOVA. Data from each follow-up will be compared to baseline scores. EPDS/GAD-7 scores will be the dependent variables, and follow-up times will be our independent variable.

Each stool sample will undergo shotgun metagenomics for taxonomic and functional output readings. A comprehensive analysis of all findings will be conducted by an experienced bioinformatics expert at Zymo Research. All researchers involved in the stool analysis will be blinded to the type of intervention. The relationship between each intervention and the relationship to EPDS and GAD-7 scores will be analyzed and reported by an experienced bioinformatician.

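### The rule letting women who stop supplements for side effects continue in the control arm, read literally, changes their arm after allocation and conflicts with the intent-to-treat approach

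*Protocol article*

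**What the plan says.** All references are to the protocol article.

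- **Criteria for study withdrawal**, on women who stop because of a reaction: "If the reasons for stopping supplements are allergic reactions or side effects, they will be withdrawn from the intervention". An adverse report follows, and then: "If participants still wish to continue with the study, they may do so as part of the control arm". Just before this, women who miss a week or more of supplements for other reasons, such as forgetting, are kept in the study with no mention of a change of arm.
- **Trial design and setting**, on what the control arm is: "Women in the control arm will receive standard care offered to all obstetric patients seen at the hospital". On who enters it: "Participants unable or unwilling to take any of our investigational products will be assigned to the active control arm". Entry is by inability or preference, not by randomization.
- **Statistical analysis**, for the continued trial: "we will use mental health scores as the primary outcome and an intent-to-treat approach for these analyses". On discontinuers: "Those who discontinue treatment will still be included". That sentence does not name the arm.
- **Outcomes measured** makes process evaluation the primary outcome, including compliance and side effects in the intervention groups.
- **Mental health outcome** summarizes and compares EPDS and GAD-7 by group.
- **Discussion** gives 75 women in the intervention arms and 25 in the control arm.

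**The concern.** An allergic reaction or side effect happens after allocation and may be caused by the product. A rule that reassigns a woman on that basis makes arm membership depend on the treatment's own effects. Intention to treat exists to prevent this.

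Three things would be affected if she were counted as a control:

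- **Randomized comparisons.** Gutopia, Gutboost and Gutless would each lose the women who tolerated the products least, so the groups compared would no longer be the groups randomized.
- **Feasibility results.** Compliance and tolerability in the intervention groups would describe only those who could take the products. Tolerability is a central question for this trial.
- **Control arm.** A small, non-randomized group on standard care would gain women who had been exposed to fish oil and probiotic or placebo.

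Under Microbiome profiling, the article plans to continue enrollment into an efficacy stage if the feasibility trial succeeds. An arm label recorded now could therefore reach the intent-to-treat comparison later, although the article does not say how feasibility-stage women would be handled.

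**Working it through.** **Text check.** The plan has no figure to reproduce on this point, so the question is whether the statements agree.

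1. The withdrawal rule places the woman in the control arm. Because that arm is defined by being unable or unwilling to take the products, a woman who has just reacted to one fits its entry description. Staff could readily record her there.
2. The rule separates her from other non-adherent women, for whom no change of arm is mentioned. The move is therefore tied to side effects, not to non-adherence in general.
3. Intent-to-treat, together with keeping discontinuers in the analysis, implies the allocated arm.
4. Steps 1 and 3 give different arms for the same woman unless the withdrawal rule is read as covering procedures only. No sentence says so.

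**Illustration of size.** Inputs from the Discussion are 75 intervention women and 25 controls. Assumed, because the documents do not give them: stop rate *s*; fraction *f* of stoppers who continue and are counted as controls; compliance *c* = 80% among women who do not stop.

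- Women stopping = 75*s*
- Share of the enlarged control group = 75*sf* / (25 + 75*sf*)
- Compliance overstatement = *c* − (1 − *s*)*c* = *sc*, if every stopper leaves the intervention denominator

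| *s* | Stops | Control share, *f* = 1 | Control share, *f* = 0.5 | Compliance overstated by |
|---|---|---|---|---|
| 0% | 0 | 0% | 0% | 0 points |
| 2% | 1.5 | 1.5/26.5 = 5.7% | 0.75/25.75 = 2.9% | 1.6 points |
| 5% | 3.75 | 3.75/28.75 = 13.0% | 1.875/26.875 = 7.0% | 4.0 points |
| 10% | 7.5 | 7.5/32.5 = 23.1% | 3.75/28.75 = 13.0% | 8.0 points |

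**Effect on EPDS.** Suppose there is no treatment effect, all stoppers continue (*m* = 75*s* women), and they score *d* points worse than everyone else. Relabelling then moves the intervention-minus-control difference in favour of intervention by *md*/(25 + *m*) + *md*/75.

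- *s* = 5%, *d* = 2: 0.26 + 0.10 = 0.36 points. With *d* = 4: 0.52 + 0.20 = 0.72 points.
- *s* = 10%, *d* = 2: 0.46 + 0.20 = 0.66 points. With *d* = 4: 0.92 + 0.40 = 1.32 points.

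The values of *d* are assumed. If stoppers scored better than the others, the direction would reverse.

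**What the documents offer on stop rates.** Under The safety profile of supplements, one fish-oil trial had no withdrawals for adverse events, and another documented no adverse events in 83 women. A third had one treatment termination for nausea, in its placebo group: 1/36 = 2.8% on 18 women per group, or 1/24 = 4.2% on its stated 24 participants. None of these is a stop rate for the products used here.

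**The case against.** The strongest reply is that the sentence is a follow-up rule, not an analysis rule. It sits among the withdrawal criteria and tells staff what a woman may do once she is off product. Control-arm care is standard care without products, and visits, questionnaires and stool samples are the same in every arm. On this reading she simply continues without supplements and is analysed as allocated. This reading is possible and agrees with Statistical analysis. It does not remove the problem, because the sentence names an arm and nothing limits it to procedures.

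Other parts of the reply stand:

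- A reader might infer that the article says she is analysed as a control, or that the withdrawal sentence is its only statement on her arm. Neither is supported. Intent-to-treat with "Those who discontinue treatment will still be included" points to the allocated arm.
- A reader might infer a second contradiction from the withdrawal section's own phrase "they will be included in all analyses consistent with the intention to treat". That phrase concerns women who miss visits and later return, so it does not bear on stopping for side effects.
- Her data are not lost. Side effects and reasons are documented, and an adverse report is made. What is uncertain is the arm in which she is counted.
- The intervention-versus-control comparison is already non-randomized, and the intent-to-treat analysis applies only if the trial continues.
- The documented evidence points to few stops, and its only termination was on placebo. Nothing in the documents supports a rate as high as 10%.

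These points limit the weight of the concern. The condensed format does not answer it, because the article states the rule and has not merely left detail to a fuller document.

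**Conclusion.** The concern holds as a conflict on the literal reading: the withdrawal rule changes a woman's arm after a possibly treatment-caused event, while the intent-to-treat approach implies that she stays in her allocated arm. The text leaves a milder reading open but does not adopt it. The sentence should be changed.

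The consequences for the randomized arms, the compliance and tolerability figures and the control arm follow only if she is actually counted as a control. Their size cannot be derived from the documents and is probably small. The percentages shown depend on assumed stop rates, an assumed fraction continuing and an assumed 80% compliance, and all are zero if nobody stops. Stopping a product on safety grounds is a clinical decision and is not criticized.

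**What to change.** Under Criteria for study withdrawal, replace the control-arm sentence with: she stops the product or products, continues visits, questionnaires and stool samples, and is counted and analysed in her allocated arm. Record which product was stopped and on what date; the reason is already documented.

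The cost is one sentence and two data fields, with slightly more data entry. It needs no extra visits or participants and leaves the safety rule as it is. With this wording the groups stay at the planned 75 and 25 however many women stop supplements.

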#### Outcomes measured

As a feasibility study, process evaluation will be our primary outcome. In the first 6 months of the trial, we will monitor the number of patients screened, randomized, and enrolled per month; the average time lapse between screening and enrollment; and the time taken to enroll 15% of our target (i.e., *n* = 15). We will also assess baseline rates of O3FA and probiotics supplementation in this specific cohort prior to randomization. We will identify and document all barriers to meeting the target numbers needed for each study arm and address them appropriately. In patients successfully enrolled, we will also monitor compliance, side effects, and challenges in taking supplements in the intervention groups. We will closely document all issues in adhering to intake instructions and attempt to resolve them on a case-by-case basis (i.e., if forgetfulness is a cause, daily automatic email reminders will be sent to that individual). In Gutopia, attaining a daily fiber target of 35 g/day will be monitored frequently via phone call in the first 6 months or until the patient no longer needs the support. Finally, we will assess retention rates, the proportion of study visits completed, and challenges related to the collection and shipment of stool samples, as well as the completion of questionnaires and dietary recall. All barriers to the timely completion of these tasks will be documented and managed on a case-by-case basis. Strategies to overcome each of these barriers will be proposed in the final write-up of this study.

As part of our secondary aims, we will seek the opportunity to produce preliminary data on the association between maternal microbial response to each intervention and self-reported scores on questionnaires of mental health challenges. This will be for exploratory purposes to identify any signals that will further support the conduct of a larger trial.

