### Randomization and baseline evaluation

All eligible patients interested in participating will be consented to and randomized or assigned to an intervention or control arm based on responses during screening. If eligible for full randomization, this will be completed by the study principal investigator using a computer-generated randomization via random permuted blocks. The study coordinator will only be informed of the status of randomization to the Gutopia arm and will be blinded to the Gutboost and Gutless arms.

Once randomized, the participant will be scheduled for the baseline assessment as soon as possible. If scheduled as a virtual visit, a stool kit will be mailed to the participant or provided at their prenatal visit. There is no predetermined time between the screening and baseline; however, the baseline visit will take place prior to the 35th gestational week (visit 2). The collection of baseline questionnaires will include the following: The Generalized Anxiety Disorder-7 (GAD-7), The Edinburgh Postnatal Depression Scale (EPDS), Single-Item Sleep Quality Scale, Pregnancy Physical Activity Questionnaire Consumer Financial Protection Bureau—Financial Wellbeing (CFPB-FWB), Demographic Questionnaire, and the Dietary Screening Form. Please see the supplementary materials for a breakdown of the versions used and the psychometric properties of each questionnaire. The baseline visit will also include the provision of a stool sample.

There will be a total of six study visits; visit 1 (baseline) and visit 2 will occur during pregnancy, with the remaining four scheduled to take place in the postpartum period (**Figure 1**). All questionnaires completed at baseline, with the exception of the CFBP-FWB, the Demographic Questionnaire, and the Dietary Screening Form, will be completed at all postpartum visits. A postdelivery questionnaire will be completed at visit 3 (~ 4–6 weeks postpartum), and a postpartum questionnaire will be completed at visits 4–6. The sessions will be 45–60 minutes in length.

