### The intervention

Participants in all intervention groups will receive a 200-ml bottle of Genestra brand Super EFA Forte Liquid Omega-3 Fatty Acid. Participants will be instructed to take 1 teaspoon a day with a meal.

Participants in the Gutopia and Gutboost intervention groups will receive HMF Maternity Probiotic Formula, a Genestra brand. Participants will be asked to take one tablet daily with food.

Details of both supplements are provided under Investigational products in the following section.

Only participants in Gutopia will receive a dietary intervention. Intervention is geared toward increasing gut-friendly foods via a flexible dietary plan aimed at increasing daily uptake of prebiotic and probiotic foods. A registered dietitian will use baseline food questionnaire data provided by each subject at enrollment to devise strategies and recommendations for increasing intake of pre/probiotic foods. The target goal is to include at least 35 g/day of fiber and at least one to two servings of fermented foods daily. The dietary intervention will also include recommendations minimizing highly processed foods high in sugar and fat. To improve adherence and accountability, weekly follow-ups by phone, virtual meeting, or email will be conducted by a trained study team member until patients have reached a level of confidence in attaining goals. During each follow-up, the study team will monitor the level of adherence to the study RD’s recommendations. These follow-ups will be designed to provide encouragement while helping patients address and prevent triggers that jeopardize their fiber intake.

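### Gutopia's extra diet contacts may raise its adverse-event counts relative to the other arms, and the article leaves unclear whether side effects are sought in the control arm.

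*Protocol article*

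**What the plan says.** All places are in the Protocol article.

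- **Contact in Gutopia only.** The intervention section gives the dietary programme to Gutopia alone and states that "weekly follow-ups by phone, virtual meeting, or email will be conducted by a trained study team member until patients have reached a level of confidence". The stated purpose is diet: at each contact "the study team will monitor the level of adherence" to the dietitian's advice. Outcomes measured adds that the fibre target is "monitored frequently via phone call in the first 6 months or until the patient no longer needs the support".
- **Contact in all arms.** Trial design and setting lists six visits, described as three-monthly. "Two of the study visits will occur during pregnancy" (enrolment and third trimester); the other four fall at 1, 3, 6 and 9 months after delivery. Beyond these visits, Outcomes measured mentions only case-by-case help with supplement intake, such as email reminders.
- **Side effects as an outcome.** Process evaluation is the primary outcome. Within it, "we will also monitor compliance, side effects, and challenges in taking supplements in the intervention groups".
- **Recording.** Criteria for study withdrawal requires every adverse event in the study to be recorded, without limiting this to any arm. Serious product-related events go to the regulator "immediately if possible and no later than 7 days after becoming aware of the information".
- **How events are sought.** The article does not say. By contrast, Concomitant therapies does state that medication, psychotherapy and natural-product use is asked about at baseline and at each follow-up visit.

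**The concern.** An event count depends on how often somebody asks or listens, as well as on how often events occur. Gutopia and Gutboost take the same two products, yet Gutopia women speak or write to staff far more often early on. A woman who mentions nausea or loose stools in a diet call has reported an adverse event, and the recording rule then requires it to be kept. A Gutboost woman with the same brief symptom may have forgotten it by her next visit. If rates are tabulated by arm, Gutopia may look less tolerable for that reason alone. The study coordinator also knows who is in Gutopia (Randomization and baseline evaluation).

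The second issue is the background rate. All three intervention arms take fish oil, so Gutboost versus Gutless isolates only the probiotic. Control is the one arm without study fish oil. If side effects are actively sought only in the intervention groups, the trial has no comparable concurrent figure for symptoms that occur without the product.

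What is at stake is one component of the primary feasibility outcome. Microbiome profiling says enrolment will continue into an efficacy trial if feasibility is shown, so any unevenness would carry forward.

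**Working it through.** **1. Number of contacts.** One month is taken as 4.35 weeks. Weekly contact for six months is 6 × 4.35 = 26.1, so at most about 26 Gutopia contacts on top of the six visits. Gutboost, Gutless and control have the six visits. The 26 is a ceiling, because contacts stop once the woman is confident or needs no more support.

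**2. Gap between visits.** The stated interval of 3 months is 3 × 4.35 = 13.0 weeks. I compared this with the listed visits, assuming delivery at week 40 and visit 2 at week 28, 32 or 35. Week 35 comes from an ambiguous sentence in Randomization and baseline evaluation, which is about the baseline visit but carries visit 2 in brackets.

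| Enrolment week | Visit 2 week | Gap from visit 1 to visit 2 (weeks) |
|---|---|---|
| 12 | 28 | 16 |
| 12 | 32 | 20 |
| 12 | 35 | 23 |
| 22 | 35 | 13 |
| 34 | 35 | 1 |

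The mean of the five gaps for enrolment at week 12 is (40 + 9 × 4.35 − 12) / 5 = 13.4 weeks, close to the stated interval. For enrolment at week 34 it is 9.0 weeks. The three-monthly description therefore holds only as an average for the earliest enrolments. For women enrolled early enough, the first gap is about 13 to 23 weeks, with 23 as the extreme; late enrolment makes it much shorter. This gap applies to the visits of every arm. What differs is that Gutopia can have up to 13 to 23 weekly contacts inside it, and the other arms have none listed.

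**3. Effect of unequal capture.** Observed rate = true rate × share captured. Both illustrations assume 25 women per arm (75 intervention women in the Discussion, split equally) and the same true rate in each arm.

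- *Illustration A, all inputs assumed.* True rate 30%; capture 90% with frequent contact and 50% at a later visit. 0.30 × 0.90 = 0.27 and 0.30 × 0.50 = 0.15. Times 25, this is 6.75 and 3.75 women, a ratio of 1.8.
- *Illustration B, true rate from the article.* In one fish-oil trial summarised under The safety profile of supplements, 10 of 18 treated women reported no event, so 8/18 = 44% did. Capture is assumed complete in Gutopia.

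| Capture in the less-contacted arm | Observed rate there | Spurious ratio | Chance of a nominally significant Gutopia excess |
|---|---|---|---|
| 90% | 40% | 1.11 | 5% |
| 70% | 31% | 1.43 | 16% |
| 50% | 22% | 2.00 | 38% |

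The last column uses a normal approximation at a two-sided 5% level, for which equal capture would give 2.5% in this direction. The 44% is only a handle: the article gives that trial 24 participants but denominators of 18 in each group.

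**4. Contrasts touched.**

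- Gutopia against any other arm: contact differs, so the comparison is exposed.
- Gutboost against Gutless: same visits, and women are blinded to probiotic or placebo, so there is no distortion from contact.
- Intervention against control: the visits match, but the side-effect outcome names only the intervention groups, so solicitation may differ.

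**5. Why a background rate matters.** In the same cited trial, 12 of 18 placebo women reported no event, so 6/18 = 33% did report one.

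**The case against.** The case on the other side is substantial. The diet contacts concern adherence, may be by email, are time-limited and are not said to ask about symptoms, so extra capture is an inference. No formal comparison of adverse-event rates is planned; the between-group analyses described concern depression and anxiety scores and the microbiome. Gutopia also differs from Gutboost in diet, so it never isolates the products. This is a condensed article that refers to a safety protocol not shown, and the full protocol may set a common enquiry.

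Most of this stands, and it rules out several stronger readings that a reader might infer:

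- *That event rates cannot be compared between any arms.* Gutboost versus Gutless is unaffected.
- *That control women have no adverse-event recording.* The recording rule has no arm limit. The sentence in Outcomes measured can be read as being about supplement tolerability, which would not apply to women given no supplement.
- *That Gutopia will look worse.* The text supports only that it may.
- *That 23 weeks is the usual gap.* It needs enrolment at week 12 and one reading of an unclear sentence.
- *That serious events go unheard for months.* The reporting clock starts at awareness, but the article does not say how women report between visits, so no delay can be derived.

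Control data would not settle the matter either. Women enter that arm because they cannot or will not take the products, so its rate is not a randomised comparator.

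What the objection does not remove is stated text: repeated staff contact in one arm only, a duty to record everything, and a side-effect outcome that names only some arms. Descriptive rates by arm would carry the same distortion as a formal test.

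**Conclusion.** The point holds in a limited form. Gutopia's additional, time-limited contacts may raise its event counts relative to Gutboost, Gutless and control, with no difference in tolerability needed. Separately, the recording rule and the side-effect outcome should be reconciled on whether events are solicited in all four arms, because control offers the only concurrent, though non-randomised, rate without study fish oil.

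The direction follows from the contact schedule if women mention symptoms in diet contacts. The size is not known. Spurious ratios of 1.11 to 2.00 correspond to assumed capture of 90% down to 50% in the less-contacted arm; the 27% versus 15% figures are likewise an illustration. None of this undermines the feasibility design. It is an avoidable weakness in one component of the primary outcome with a cheap remedy.

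**What to change.** In Outcomes measured, state that adverse events are solicited in all four arms with one common short form, at the same times in each arm: at least at every scheduled visit, and optionally at a fixed interval between visits. REDCap already carries the participant questionnaires (Data management), so no new system is needed. Base any summary of event rates by arm on that form alone, and list events first heard in Gutopia diet contacts separately. Align the wording with Criteria for study withdrawal, so that every event from any source is still recorded and reported for safety as that section requires.

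Cost: protocol wording, one form, a few minutes of each participant's time per form, and some staff time to follow up positive answers. At visits only, this is at most 6 × 100 = 600 forms. A monthly form from week 12 to 9 months postpartum would be about (40 − 12) / 4.35 + 9 ≈ 15 per woman, or up to roughly 1,500 in total. The visit-only version is the economical minimum; the monthly version lessens recall loss over the long first gap.
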